The investigator will provide a multidimensional behavioral therapy (speech pathology therapy) guideline, which is a non-pharmacological treatment for cough, to all participants and educate the participants about this therapy [15]. This includes the creation of awareness that repetitive coughing is not beneficial and that coughing can be controlled by oneself through the suppression of the cough reflex that is induced by stimuli by swallowing saliva or water, or breathing with pursed lips when about to cough [15]. In addition, the education includes the vocal hygiene method, which ensures the supply of moisture to reduce laryngeal irritation, and psychological education counseling therapy, which helps patients recognize that chronic cough is difficult to treat and thereby set realistic treatment goals [15].

During the clinical trial period, new intake of any prescription drugs and over-the-counter medicines, except for investigational products and drugs allowed at screening visit, should be avoided. In particular, the trial should be discontinued if the following medications or treatments are required due to the participants’ circumstances or clinical condition: ACE inhibitor, DPP-4 inhibitor, antitussive, expectorants, steroid, antileukotrienes, anticholinergic, LABA, oral antihistamines, traditional Korean treatment (e.g., herbal medicine, acupuncture, etc.) to improve chronic cough, and other drugs or treatments that, in the investigator’s judgment, may affect the results of the clinical trial. 

At any time during the trial, the participants can voluntarily withdraw their participation for reasons such as dissatisfaction with the treatment effect. If participants are no longer able to participate in the trial due to adverse events or intercurrent diseases during the trial or have received the contraindicated drugs, which may affect the research outcomes, the participants will be dropped from the study at the investigators’ discretion. 

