### 2.9. Economic Evaluation

Economic evaluation will be conducted along with the randomized controlled trial (RCT) for feasibility, effectiveness, and safety. The cost-effectiveness of *Maekmundong-tang* will be estimated compared to *Saengmaek-san*, in regard to the healthcare system and societal perspective.

Medical, non-medical (transportation, time, and nursing care costs), and productivity loss costs due to participants’ chronic cough during the trial period will be estimated using the cost questionnaires, institutional data, and if necessary, data from Statistics Korea. Especially, productivity loss will be assessed using the Work Productivity and Activity Impairment Questionnaire: General Health V2.0 [30,31]. With regard to the effectiveness data, trial outcome measures, including EQ-5D-5L/EQ-VAS, CSS, and cough VAS, will be determined and, thereby, the incremental cost–utility ratio and the incremental cost-effectiveness ratio between *Maekmundong-tang* and *Saengmaek-san* will be calculated. 

The analysis period is based on the clinical trial period, and for participants who drop out, data will be collected until the end of the administration of the investigational product for each participant. However, if an individual participant drops out due to an adverse event or intercurrent disease during the clinical trial, or due to aggravation of cough symptoms, a telephonic follow-up will be conducted at Week 24 with the consent of the participants and without being excluded from the data collection of the economic evaluation study. If necessary, one-way sensitivity analysis will be performed for possible variables, a tornado diagram will be presented, and a probability sensitivity analysis will be performed using the distribution and representative values of variables. In addition, if necessary, subgroup analysis can be performed according to the subgroup analysis plan of the trial. If the full yield cost and effectiveness outcomes of interventions during the trial period cannot be observed, a decision-analytic model will be developed to conduct a long-term evaluation. 

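### Whether a dropout's costs and utilities are followed to Week 24 depends on the reason for leaving, so economic data are selectively missing by design

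*Protocol article*

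**What the plan says.** Section 2.9 sets the horizon: "The analysis period is based on the clinical trial period". Section 2.1 and Table 1 extend that period to a Week 24 telephone contact, made for the economic evaluation, at which EQ-5D-5L/EQ-VAS, CSS, cough VAS and the cost questionnaire are collected. These feed the incremental cost-utility and cost-effectiveness ratios, since "trial outcome measures, including EQ-5D-5L/EQ-VAS, CSS, and cough VAS, will be determined" as the effectiveness data.

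For dropouts, section 2.9 gives two rules:

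- Default: "for participants who drop out, data will be collected until the end of the administration of the investigational product for each participant".
- Exception: "if an individual participant drops out due to an adverse event or intercurrent disease during the clinical trial, or due to aggravation of cough symptoms", then "a telephonic follow-up will be conducted at Week 24 with the consent of the participants and without being excluded from the data collection".

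Other routes out of the trial are not named in the exception:

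- medication compliance below 70% at Week 6 (section 2.5);
- a cough diary less than 70% complete (section 2.6.2);
- voluntary withdrawal, since participants "can voluntarily withdraw their participation for reasons such as dissatisfaction with the treatment effect" (section 2.5);
- need for a listed drug or treatment, where "the trial should be discontinued if the following medications or treatments are required" (section 2.5). Dropping a participant who has received a contraindicated drug is at the investigators' discretion.

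**The concern.** The ratios are meant to describe costs and effects over 24 weeks, but for some dropouts the plan chooses not to collect the last 18 weeks or more, and the choice turns on why they left. Those reasons are unlikely to be neutral. A participant who leaves dissatisfied may have a different utility, and may spend differently on other care afterwards, from one who leaves because of an adverse event. The observed data then mix people followed for 24 weeks with people followed for 6 or fewer, selected by a variable that may relate to both cost and outcome.

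This is a rule of data collection. An analysis plan can say how to handle missing values, but it cannot recover a Week 24 interview that was never attempted. Any imputation for the truncated dropouts would have to borrow from completers and from dropouts of a different kind. The article's conclusions expect the cost-effectiveness comparison to support expansion of insurance coverage, so the result has an intended use.

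**Working it through.** **Inputs**

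- Dosing lasts 6 weeks and the horizon is 24 weeks (section 2.1, Table 1).
- Sample size is 24 evaluable, 20% dropout, 30 in total, 15 per arm (section 2.7).

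**The plan's own figure.** 24 / (1 − 0.20) = 30, or 12 / 0.80 = 15 per arm. It reproduces, and implies 30 × 0.20 = 6 dropouts.

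**Time lost per dropout under the default rule**

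- Dosing ends at Week 6: 6/24 = 25% observed, 18 weeks lost.
- Dosing ends at Week 3 (assumed early stop): 3/24 = 12.5% observed, 21 weeks lost.

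The end of administration could mean the participant's actual last dose or the scheduled end. On either reading, collection stops by about Week 6.

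**Time lost in the trial.** Full follow-up is 30 × 24 = 720 person-weeks. The 24 completers give 24 × 24 = 576. How many dropouts meet the exception is not known, so two cases are shown, with all dropouts assumed to stop dosing at the same week.

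| Dropouts meeting the exception | Dosing ends | Observable person-weeks | Unobserved |
|---|---|---|---|
| 0 of 6 | Week 6 | 576 + 6×6 = 612 | 108/720 = 15% |
| 0 of 6 | Week 3 | 576 + 6×3 = 594 | 126/720 = 17.5% |
| 3 of 6 | Week 6 | 576 + 3×24 + 3×6 = 666 | 54/720 = 7.5% |
| 3 of 6 | Week 3 | 576 + 3×24 + 3×3 = 657 | 63/720 = 8.75% |

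The last two rows credit excepted dropouts with all 24 weeks. That is generous: they get one call, subject to consent, and section 2.9 states no assessments for them between dropout and that call.

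**Which routes fall where.** Low compliance and an incomplete diary are outside the exception unless the underlying cause is one of the three listed. So is voluntary withdrawal. Contraindicated drug use is unclear: if the drug was needed because cough worsened, the participant may be classed as excepted; otherwise not. The article does not say who decides.

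**The case against.** Two stronger readings are tempting, and neither is supported.

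*That the participants who spend money on cough treatment are the very ones whose later costs go uncollected.* A reader might infer this because the drug restriction covers the whole trial period, including the 18 weeks off treatment. But someone who needs an antitussive or steroid for worse cough plausibly meets the exception, and dropping for contraindicated drugs is discretionary. Table 1 also has no contact between the Week 9 visit and the Week 24 call, so after Week 9 there is no scheduled point at which such use would be found and lead to truncation. At the Week 24 call itself, the cost questionnaire is administered. The realistic exposure is dropout up to Week 9.

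*That a definite QALY bias follows.* At an assumed utility of 0.85, one extra dropout truncated at Week 6 in an arm of 15 would shift that arm's mean by 0.85 × (18/52) / 15 = 0.0196 QALY (0.017 to 0.022 for utilities 0.75 to 0.95). That holds only if unobserved weeks score zero, which the protocol nowhere says. The difference between arms is nil if reasons split equally, and the rule is the same in both arms of a blinded trial. The article does not use the term QALY; it is inferred from the cost-utility ratio and EQ-5D-5L.

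It can also be said that section 2.9 allows sensitivity analyses, and a decision-analytic model if outcomes in the trial period cannot be fully observed; that missing-data methods belong in an analysis plan; and that the economic evaluation is exploratory, within a feasibility trial. The last point stands and limits the weight of this one. The others do not remove it: a model or an imputation substitutes assumptions for data that a telephone call could have supplied.

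**Conclusion.** The point holds as a flaw in data collection. The plan sets a 24-week economic horizon and then, for dropouts outside three listed reasons, stops collecting at about Week 6 or earlier. Missing cost and utility data therefore depend on the reason for leaving. At the planned 20% dropout, the loss is up to 15% of person-weeks if dosing ended at Week 6, or 17.5% if it ended at Week 3. Both figures assume that no dropout meets the exception; the loss is about half if three of six do.

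No direction or size of bias in the incremental ratios is claimed. Both depend on the unknown split of reasons between arms and on the handling of missing data, which is not shown. The feasibility outcomes and the Week 6 CSS comparison do not depend on this rule. It should be fixed because it is cheap and the data cannot be recovered later, but it does not threaten the trial's main purpose.

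**What to change.** In section 2.9, replace the two dropout rules with one. Every randomised participant who has not withdrawn consent to contact is offered the Week 24 telephone follow-up, whatever the reason for leaving. The call collects EQ-5D-5L/EQ-VAS, CSS, cough VAS and the cost questionnaire, with the cost questions covering the period since last contact. All participants are analysed over the same 24-week horizon. The method for remaining missing values can be left to the analysis plan.

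The cost is at most about six extra calls at the planned dropout rate, fewer to the extent that some dropouts are already covered by the exception, plus protocol and consent wording. Some dropouts will decline. One call does not restore interim EQ-5D-5L assessments missed between dropout and Week 24, so the course of utility in between stays unobserved, and costs are recalled over a longer period. No treatment or stopping rule changes, and those telephoned still count as dropouts for the completion and dropout rates.

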### 2.5. Interventions

All investigational drugs were manufactured by Kyungbang New Pharmaceutical Co., Ltd. (Incheon, Republic of Korea) in compliance with the 2021 Korean Good Manufacturing Practice guidelines. All participants will be allocated to the *Maekmundong-tang* or *Saengmaek-san* groups. Each 2.5-g serving of *Maekmundong-tang* granule (Yunpye-tang extract granule, Maekmundong-tang; product code: 200005808) comprises grayish-brown granules that consist of 1250 mg *Maekmundong-tang* dry extract, 625 mg corn starch, and 625 mg lactose hydrate. The raw materials and composition of *Maekmundong-tang* dry extract 1250 mg are as follows: Liriopis seu Ophiopogonis Tuber 3.33 g, Pinelliae Tuber 1.67 g, Oryzae Semen 3.33 g, Zizyphi Fructus 1.00 g, Ginseng Radix 0.67 g, and Glycyrrhizae Radix et Rhizoma 0.67 g. Similarly, each 1.41 g serving of *Saengmaek-san* powder (Kyungbang *Saengmaek-san*, mixed single extract; product code: 200005617), the active control drug, is a brown powder that consists of 0.75 g Liriopis seu Ophiopogonis Tuber extract, 0.30 g Ginseng Radix extract, and 0.36 g Schisandrae Fructus extract. The investigator will instruct all participants to orally consume 1 pack of the formulation 3 times a day, before or between meals, for 6 weeks. Each of the herbal medicine was produced simultaneously in one batch and therefore has the same batch number. Their expiration date is 36 months from the date of manufacture. They should be stored in airtight containers at room temperature (1–30 °C). 

To improve the compliance of the participants of the clinical trial, the investigator will check the participant’s investigational product intake during the administration period and record details of compliance in the case report form (CRF); participants with less than 70% medication compliance at Week 6 will be dropped out.

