#### 2.6.2. Effectiveness Outcomes

The primary effectiveness outcome is the CSS score at Week 6. The CSS is a scale for the subjective assessment of cough severity and frequency that is reported by the patient during the daytime (08:00–20:00) and nighttime (20:00–08:00), and each subdomain of the scale is assigned 6 points, from 0 to 5. The total score is calculated as the sum of the daytime and nighttime scores (0–10 points) [19]. The validity and replicability of the Korean version of CSS have been verified [20]. Until Week 9, participants will be instructed to self-evaluate the CSS twice a day and record the score in a cough diary. During the telephonic follow-up survey (Week 24), participants will be asked to respond on their cough symptoms during the daytime and nighttime of the previous day. For statistical analysis, the average value (total, daytime, and nighttime scores) of the CSS since the previous visit that has been recorded in the cough diary and will be collected at each visit (excluding the baseline visit) will be used, and the average value of the previous 7 days will be used for determining the status at the baseline visit. The investigator will educate the participants on how to write a cough diary at every visit and attempt to minimize omissions in records. If less than 70% of the cough diary distributed at each visit has been completed, the participant will be dropped out.

The secondary outcome measures include the CSS (at weeks 3, 9, and 24), cough visual analog scale (VAS), the Leicester Cough Questionnaire (LCQ), the Hull Airway Reflux Questionnaire (HARQ), Integrative Medicine Outcome Scale (IMOS), Integrative Medicine Patient Satisfaction Scale (IMPSS), a five-level version of the EuroQol Five-dimensional Descriptive System (EQ-5D-5L), the EuroQol visual analog scale (EQ-VAS), yin deficiency score, and serum biomarkers.

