### 2.7. Sample-Size Calculation

This is the first exploratory clinical trial to evaluate the feasibility and preliminary effect of *Maekmundong-tang* administration in patients with nonspecific chronic cough. Therefore, there are no prior literature references for sample size calculation. Referring to a study that recommended a minimum of 12 people per group in a preliminary study in the field of life sciences [28], a total of 24 participants, with 12 participants per group, are needed. Considering a dropout rate of 20%, a total of 30 participants, 15 in each group, were specified as the target sample size.

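### Section 2.9 keeps the Week 24 economic survey for only three dropout reasons; participants who leave by other named routes have no cost or utility data for at least 18 of 24 weeks

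*Protocol article*

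**What the plan says.** Section 2.9 bases the economic analysis on the trial period, and Section 2.1 gives the economic evaluation as the purpose of the Week 24 telephone contact. For people who leave early, the default in Section 2.9 is: "for participants who drop out, data will be collected until the end of the administration of the investigational product for each participant". Dosing lasts 6 weeks, so collection ends at Week 6 at the latest.

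The same paragraph makes one exception. The Week 24 call still takes place, with consent, "if an individual participant drops out due to an adverse event or intercurrent disease during the clinical trial, or due to aggravation of cough symptoms".

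The article names four further ways out:

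- **Dissatisfaction** (Section 2.5): "the participants can voluntarily withdraw their participation for reasons such as dissatisfaction with the treatment effect".
- **Low compliance** (Section 2.5): "participants with less than 70% medication compliance at Week 6 will be dropped out".
- **Incomplete diary** (Section 2.6.2): "If less than 70% of the cough diary distributed at each visit has been completed, the participant will be dropped out".
- **Prohibited treatment** (Section 2.5): "the trial should be discontinued if the following medications or treatments are required due to the participants’ circumstances or clinical condition". For those who have received such drugs, "the participants will be dropped from the study at the investigators’ discretion".

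None of these four is on the exception list.

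**The concern.** The rule makes the availability of late economic data depend on why a participant left. Two of the four uncovered exits are plausibly tied to outcome. Someone dissatisfied with the effect may have a cough that is unchanged, and an unchanged cough is not a worsened one. Someone who needs another cough treatment has, almost by definition, further costs and perhaps a different later utility. The other two exits, compliance and diary, are imposed by the trial on people who need not have withdrawn consent and could still be reached by telephone.

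At stake are the incremental cost-utility and cost-effectiveness ratios. If the uncovered exits occur at different rates, or in different kinds of patient, in the two arms, the ratios compare selected groups after Week 6. Some difference by arm is conceivable: Section 2.5 describes 2.5 g of granules against 1.41 g of powder, three times a day, which could affect compliance. That is an inference and not something the article states. The evaluation is exploratory, but Section 4 expects it to inform insurance coverage. The full analysis set in Section 2.8 keeps all data obtained; it cannot supply data that were never sought.

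**Working it through.** **Inputs**

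- Economic horizon: 24 weeks (Section 2.1, Table 1).
- Dosing: 6 weeks (Section 2.1).
- Cost questionnaire and EQ-5D-5L: Weeks 0, 3, 6, 9 and 24, so 5 assessments (Table 1).
- Sample size: 24 needed (12 per group), 20% dropout, target 30 (15 per group) (Section 2.7).

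**The plan's own figure.** 24 / (1 − 0.20) = 30, and 12 / (1 − 0.20) = 15 per group. The stated target reproduces.

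**Loss per participant outside the exception.** Weeks lost = 24 − stop week; fraction = weeks lost / 24; assessments lost = those scheduled after the stop.

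| Data end at | Weeks lost | Share of horizon | Assessments lost |
|---|---|---|---|
| Week 6 (dosing completed) | 24 − 6 = 18 | 75% | 2 of 5 |
| Week 3 | 24 − 3 = 21 | 87.5% | 3 of 5 |
| Soon after Week 0 | up to 24 | up to 100% | 4 of 5 |
| Week 9 (lenient reading) | 24 − 9 = 15 | 62.5% | 1 of 5 |

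The last row applies if someone dropped at the Week 9 visit, for example for the diary, has that visit's questionnaires kept. The stated rule does not provide for this, but it is a reasonable reading.

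**Trial level.** Planned dropouts: 0.20 × 30 = 6, or 0.20 × 15 = 3 per arm. Planned participant-weeks: 30 × 24 = 720. Let k be the number of dropouts outside the exception. The article does not give the split by reason, so k from 0 to 6 is an assumption. If each completed dosing (18 weeks lost):

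| k | Participant-weeks lost | Participants without Week 24 data |
|---|---|---|
| 0 | 0 | 0 |
| 1 | 18 / 720 = 2.5% | 1 / 30 = 3.3% |
| 3 | 54 / 720 = 7.5% | 3 / 30 = 10% |
| 6 | 108 / 720 = 15% | 6 / 30 = 20% |

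If dosing stopped earlier, the participant-weeks lost rise. No effect on the ratios can be computed, because the article gives no cost, utility or exit rate by arm.

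**The case against.** Several points on the other side have force.

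**Time is not the same as data.** A reader might infer that these participants lose most of their cost and utility data. For someone who completes dosing, that holds for follow-up time but not for assessments: 3 of 5 are kept. This matters most for the compliance exit, which operates at Week 6.

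**The recoverable exits are the less informative ones.** Some dissatisfied participants will decline any further contact, so no rule recovers them. Prohibited treatment can overlap with intercurrent disease or worsening cough, which are already followed; what remains is mainly treatment of an unchanged cough, probably a small group. The compliance and diary exits are the easiest to follow, but their link with outcome is less clear. This limits the expected gain. It does not explain why people removed by the trial itself should not be called.

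**Other provisions exist.** Section 2.9 also draws on institutional data for costs, allows sensitivity analyses where needed, and mentions a decision-analytic model. Institutional data may recover some costs, but not Week 24 utility. The sensitivity analyses vary inputs, and the model is meant for long-term evaluation. Handling of missing values may properly sit in an analysis plan not shown, but the point here is a stated collection rule.

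**The stakes are modest.** Feasibility is the primary purpose, and with 15 per arm the ratios will be imprecise in any case. That stands.

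Two further readings are tempting but not supported. One is that the rule biases the comparison towards a particular arm: the article gives nothing from which to tell the direction. The other is that it damages the primary effectiveness result: the CSS outcome is at Week 6, and this rule concerns economic data after dosing.

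**Conclusion.** The point holds as a correctable weakness in a stated collection rule. For participants outside the three excepted reasons, the rule forgoes at least 75% of the 24-week horizon, or 2 or more of 5 scheduled assessments; on the lenient Week 9 reading the loss is 62.5% and 1 of 5. At trial level the extent lies between nothing and 6 of 30 participants without Week 24 data. That range rests on the planned 20% dropout being realised and on an unknown split by reason. Distortion of the exploratory ratios further requires that the uncovered exits differ by arm in number or kind, which is possible but not shown. The case for change rests on the small cost of the remedy and on the fact that uncollected data cannot be restored later, not on a demonstrated bias.

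**What to change.** Change Section 2.9 so that the Week 24 telephone survey is sought, with consent, from all randomised participants whatever their reason for stopping. It should cover the cost questionnaire, EQ-5D-5L/EQ-VAS, CSS and cough VAS, and it should record any use of other cough treatment. Because these participants may have missed the Week 9 visit, the cost questions should reach back to their last contact.

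Nothing else needs to change. The completion and dropout definitions in Section 2.6.1 and the treatment rule in Section 2.5 can stay. A wider remedy that also required Week 9 CSS is not advisable: before Week 24 that score comes from the twice-daily diary, so dropouts, including those removed for not keeping it, would have to continue it. At Week 24 the CSS is asked by telephone about the previous day and needs no diary.

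The cost is a change to one rule, no new core instrument, and at most about 6 extra calls at the planned dropout. Some withdrawers will decline. Week 24 scores for those reached will include the effect of any other treatment, so that use should be reported by arm beside the results.
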